## Methods/design

2

This is a pilot randomized controlled trial for 3 years. In this study, a total of 102 participants will be enrolled, including 72 patients with recurrent PV, 15 healthy volunteers and 15 patients with psoriasis vulgaris who have recovered for more than 1 year. The entire trial consists of an initial assessment, a one-week screening phase (week 1), an 8-week observation phase (week 1 to week 8) and a 52-week follow-up phase (week 9 to week 60) (Fig. 1).

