**Figure 1 F1:**
[figure not shown]
Test flow chart.

Potential participants will be invited to an initial assessment (first visit) consisting of an inclusion and exclusion criteria screening. If eligible, participants will be asked for informed consent and will undergo assessment of Psoriasis area severity index (PASI), dermatology life quality index (DQOLS), and score of Pruritus Degree by PGA, lesion photos and vital signs, full blood count, kidney and liver function blood tests, electrocardiogram, stool examination and urine (routine chemical examinations).

A total of 72 patients with recurrent PV will be randomized (in a 1:1 ratio) to receive oral Chinese herbal medicine JWLXXF or oral acitretin for 8 weeks. During the observation phase, psoriasis symptom measures will be self-reported by participants and recorded in a daily or weekly diary. Face-to-face assessments with blinded assessors will be scheduled at weeks 2, 4, 6, and 8 (Fifth visit), with further data collected, including assessment of PASI, DQOLS, and score of Pruritus degree by PGA, lesion photos, drug adherence, vital signs, adverse events and cause analysis of shedding (Table 1). The conversation will be made to 72 patients, at the time of medical treatment, to check adherence to the dosage guidelines and to monitor adverse events. Routine chemical examinations, laboratory assessments of efficacy and safety evaluation will also be scheduled at the end of the 8-week period.

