## Setting and participants

3

There are 3 types of subjects in this study: 72 patients with recurrent PV, 15 healthy volunteers and 15 patients with psoriasis vulgaris, who have recovered for more than 1 year.

The recruitment will be performed through posters in local newspapers and hospitals and participants might also be invited to contact trial coordinators via their treating physicians (general practitioners, dermatologists, or immunologists). Research assistants will introduce and discuss the trial to potential subjects. They will be given a consent form and separate information sheets, including information on the main aspects of the trial. Patients will then be able to have an informed discussion with their family and participating consultants. The research assistants will obtain the signed consent from patients willing to participate in the trial.

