### Statistical analysis

3.10

SPSS Statistics 17.0 (IBM SPSS Inc., Armonk, NY) will be used for the statistical analysis of data, which will be carried out by independent statisticians. The Chi-square test will be used to evaluate the basic baseline characteristics and primary outcomes of the 2 groups. The Spearman rank correlation analysis of the correlation between PASI and biochemical indexes, will be used. The secondary outcomes will be evaluated by means, standard deviations and medians. The one way ANOVA test will be used to compare the mean of multiple samples, the LSD test for the homogeneous variance, and the Tamhane T2 test for the uneven variance. *P* < .05 will be considered as statistically significant.

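### The overall test for comparing more than two groups is an ordinary one-way ANOVA; uneven variances are handled only at the pairwise step, although group sizes are very unequal

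*Protocol article*

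**What the plan says.** Section 3.10 (Statistical analysis) of the protocol article gives the chi-square test to the comparison of the two groups, Spearman correlation to PASI against the biochemical indexes, and one-way ANOVA to anything with several samples: "The one way ANOVA test will be used to compare the mean of multiple samples, the LSD test for the homogeneous variance". The same sentence closes by assigning a different pairwise method to the other case: "the Tamhane T2 test for the uneven variance". A P value below .05 "will be considered as statistically significant".

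Section 2 (Methods/design) lists the subjects as "72 patients with recurrent PV, 15 healthy volunteers and 15 patients with psoriasis vulgaris who have recovered for more than 1 year", and section 3 (Setting and participants) repeats these numbers. The text under Figure 1 adds that the patients are split between two treatments: "A total of 72 patients with recurrent PV will be randomized (in a 1:1 ratio"), which makes two arms of 36.

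The article does not say which groups enter the ANOVA, whether the pairwise tests are read only after a significant overall F, or how variances are judged even or uneven. It gives no SD for any marker in any group.

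**The concern.** The plan expects that variances may differ, since it names a pairwise method for that case. The overall test has no such version: neither Welch's nor the Brown-Forsythe ANOVA is named. The ordinary F divides by a pooled variance, which is dominated by the largest group. With sizes as unequal as 72 to 15, unequal SDs make that denominator wrong in a predictable direction:

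- If the large patient group is the more variable, the denominator is too big and the test rejects too rarely.
- If the small groups are the more variable, the denominator is too small and the test rejects too often.

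At stake are the comparisons of cell counts, transcription factors and cytokines across recurrent patients, recovered patients and healthy volunteers. An overall P value could mislead in either direction. If the pairwise tests are read only after a significant F, true differences could also be lost.

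**Working it through.** **Inputs from the article.** Nominal level 5% (section 3.10). Group sizes 72, 15 and 15 (sections 2 and 3), or 36, 36, 15 and 15 with the arms kept apart.

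**Inputs assumed.** Normal data and SD ratios of 1, 1.5 and 2 between patients and the two small groups. The article gives no SDs, so these are illustrations.

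**Step 1: direction of the error.** With equal true means, N subjects and k groups,

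- E(MS between) = Σ(N − nᵢ)σᵢ² / [N(k − 1)]
- E(MS within) = Σ(nᵢ − 1)σᵢ² / (N − k)

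A valid F needs these two to be equal.

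| Groups | SDs | E(MS between) | E(MS within) | Ratio |
|---|---|---|---|---|
| 72/15/15 | 2/1/1 | (30·4 + 87 + 87)/204 = 1.44 | (71·4 + 14 + 14)/99 = 3.15 | 0.46 |
| 72/15/15 | 1/2/2 | (30 + 87·4 + 87·4)/204 = 3.56 | (71 + 14·4 + 14·4)/99 = 1.85 | 1.93 |
| 36/36/15/15 | 2/2/1/1 | (2·66·4 + 2·87)/306 = 2.29 | (2·35·4 + 2·14)/98 = 3.14 | 0.73 |
| 36/36/15/15 | 1/1/2/2 | (2·66 + 2·87·4)/306 = 2.71 | (2·35 + 2·14·4)/98 = 1.86 | 1.46 |

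The F is about half its proper size in the first row and almost double in the second.

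**Step 2: true size at nominal 5%.** Simulation, 100,000 runs per setting. With equal SDs, the plan's own 5% is reproduced: 4.9% for 72/15/15 and 5.0% for 36/36/15/15.

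| Groups | SD ratio | Patients more variable | Small groups more variable |
|---|---|---|---|
| 72/15/15 | 1.5 | 1.0% | 13.8% |
| 72/15/15 | 2 | 0.28% | 20.9% |
| 36/36/15/15 | 1.5 | 2.8% | 10.6% |
| 36/36/15/15 | 2 | 2.4% | 15.4% |

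Welch's F stays between 4.9% and 5.3% in these settings.

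**Step 3: what Tamhane T2 does.** T2 is taken as pairwise Welch t tests with a Sidak adjustment. At SD ratio 2 its family-wise error is 4.5% (patients more variable) and 4.4% (small groups more variable) for 72/15/15, and 4.2% and 3.8% for 36/36/15/15. If T2 is read only after a significant F, the 72/15/15 rates are 0.28% and 4.4%. The 21% therefore does not pass into the pairwise conclusions. In that setting the F is significant while T2 finds nothing in about 20.7% − 4.4% = 16.3% of null runs.

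**Step 4: power.** Patient SD twice the control SD, patients shifted by one control SD.

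| Groups | T2 only after significant F | T2 alone | Welch's F |
|---|---|---|---|
| 72/15/15 | 59% | 81% | 83% |
| 36/36/15/15 | 52% | 70% | 78% |

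The gate costs 81 − 59 = 22 points, or 70 − 52 = 18 points.

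**Step 5: reaching the T2 branch.** If variances are judged by Levene's test (an assumption), for 72/15/15 it rejects in about 94% of runs at SDs 2/1/1, but in only about 50% to 60% at a 1.5-fold ratio. In the other runs pooled LSD would be used although the variances differ.

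**The case against.** The strongest reply is that the plan already covers unequal variances. Tamhane T2 is assigned to that case, would usually be reached at a twofold ratio, holds the family-wise error below 5%, and on its own has nearly the power of Welch's F for 72/15/15 (81% against 83%). That stands. It confines the excess false positives to the overall P value, and it means the power loss needs two conditions together: patients are the more variable group, and T2 is read only after a significant F. The article does not state such a gate. It does not exclude one either, and ANOVA followed by LSD or T2 is commonly read as a sequence.

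It also stands that the article does not fix 72/15/15 as the groups, that no SDs are given, and that with equal SDs the F behaves as intended.

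A reader might infer more than this:

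- **That the plan's error rate is 0.3% to 21%.** Those figures need an assumed twofold SD ratio, the 72/15/15 grouping, and a conclusion drawn from the overall F.
- **That real marker differences will be missed.** That is conditional, as above; in the opposite direction the F is too liberal, not insensitive.
- **That the markers need log transformation because the plan uses Spearman correlation elsewhere.** Choosing a rank correlation does not establish a lognormal distribution, and a power contrast that changes both the scale and the test says nothing specific about variances.

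The variant of an ANOVA could be left to an analysis plan that is not shown. But the article does fix the test, and it deals with uneven variances at one step only.

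**Conclusion.** The point holds in limited form. The only overall test named for more than two groups is not protected against unequal variances, and the group sizes are unequal enough for this to matter. At an assumed twofold SD ratio its size is about 0.3% or 21% (72/15/15), or 2.4% or 15% (36/36/15/15), against about 5% for Welch's F. At a 1.5-fold ratio with patients more variable it is about 1% for 72/15/15.

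The false-positive side stops at the overall P value, because T2 holds the pairwise error near 4%. The lost power, about 18 to 22 points in the example, arises only if patients are the more variable and T2 depends on a significant F. All of this rests on assumed SD ratios and normal data. The chi-square comparison of the two randomised arms is not touched. The change is worth making because it is cheap; it is not a flaw in the trial's main comparison.

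**What to change.** In section 3.10, state that:

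1. comparisons of more than two groups use Welch's ANOVA for the overall test;
2. pairwise comparisons use an unequal-variance method (Tamhane T2, already named, or Games-Howell), and depend neither on a significant classical F nor on a preliminary test of variances;
3. the groups compared are named: patients pooled (72/15/15) or by arm (36/36/15/15).

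No change of measurement scale is needed for this. The cost is a sentence or two of wording and, if variances are in fact equal, about 2 to 4 points of power for the overall test (for example 91% to 89%, or 68% to 64%, for 72/15/15).

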## Discussion

4

### Prescription selection basis

4.1

Chinese herbal medicine has a long history in Asia and several in vivo studies, related to psoriasis, have also proved that Chinese herbal medicine has the advantages of prolonging the remission period, with lower side effects and a reduced recurrence. However, the exact mechanism of its action is still unclear and the impact on recurrence rate has not been confirmed. Our previous study showed that the JWLXXF compound was used to treat 30 cases of psoriasis vulgaris in the progressive stage of blood heat syndrome.^[14]^ After 2 courses of treatment, 22 cases were remarkably effective, 7 cases were partially effective, and 1 case was ineffective. The total significant efficiency rate was 73.33% and the total efficiency rate was 96.67%. After performing statistics, the curative effect is slightly better than that of the compound Qingdai capsule group. Modern pharmacology shows that the JWLXXF compound is mainly aimed at the pathogenesis and pathological changes of psoriasis. The main drugs have anti-inflammatory effects. Rehmannia, buffalo horn, Hedyotis diffusa and Glycyrrhiza also have immunomodulatory effects. Peony skin, Hedyotis diffusa, Forsythia suspense and Glycyrrhiza affect tumors by providing tumor growth resistance. For example, Glycyrrhiza can inhibit tumors by reducing the level of TNF-α. In addition, Bombyx mori and mulberry leaves can reduce blood sugar; Ligustrum lucidum can adjust blood lipid; and Ligustrum lucidum and Eclipta can protect the liver.^[15,16,17,18,19,20,21,22,23,24,25,26,27,28]^ Later experimental studies also showed that the mechanism of JWLXXF may be achieved by inhibiting KC keratinization, providing anti-inflammatory benefit, inhibiting PCNA and regulating TNF-α. Therefore, JWLXXF is a result of a combination of clinical experience, pharmacological and scientific research.

### Clinical efficacy evaluation basis

4.2

For moderate and severe psoriasis, PASI score is still the “gold standard” to evaluate the severity of psoriasis.^[29]^ According to the research, patients with sustained and efficient response to PASI score have a better quality of life score.^[30]^ According to the requirements of the new drug effective standard, after three months of test, the effective standard is a 75% improvement of the PASI score, which is called PASI75.^[29]^ PASI75 combined, with the pruritus score and DQOLS, can evaluate the short-term efficacy of JWLXXF. It needs a certain time to follow up on the recurrence rate and remission period to determine the long-term effect. After 8 weeks of treatment, patients with a pai75 will be followed up and this period will start from the end of the treatment. If there is no recurrence, the follow-up period is 1 year. If there is recurrence, the recurrence of the disease is the end point of the follow-up.

According to the guiding principles for clinical research on new drugs of traditional Chinese medicine (Part III), issued by the Ministry of health in 1997 and the directions of new drugs clinical research (try out) issued by the State Food and Drug Administration in 2002, the recurrence criteria are: new skin lesions appear in the patients who are cured clinically, or the original skin lesions expand, turn red, scale increase, and PASI score increase for ≥1. No recurrence criteria: the same as that at the end of treatment, but with limited skin lesions.^[31]^

### Test technology design basis

4.3

From the cellular, molecular, proteic and genomic perspectives, the mechanism of the JWLXXF compound in the treatment of psoriasis and its role in recurrence prevention was discussed. The target of the drug was comprehensively analyzed, so that the experiments could complement and confirm each other. ELISA, WB and PCR technologies are the basic means of scientific research and application in dermatology. The method of liquid-phase protein chip organically integrates microsphere, laser detection technology, fluid dynamics, high-speed digital signal processing system and computer operation function. Not only the detection speed is very fast, but it also provides specificity and sensitivity in immunodiagnosis and protein molecular interaction analysis that are often beyond the conventional technology.

### Trial status

4.4

The recruitment phase began in April 2019. Thus far, 60 patients have been recruited. The estimated end date for this study is December 2019.

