**Table 1 T1:**
[figure not shown]
Evaluation measures and time points.

The 72 patients with recurrent PV, whose PASI scores improvement are more than 75%, will undergo a 52-week follow-up phase (week 9 to week 60), with further data collection, including assessment of PASI, routine chemical examinations, recurrence rate, remission period (This remission period - the last remission period) (Table 1).

For the 52-week follow-up phase, participants will continue to record symptoms in their daily or weekly diaries. At week 60, participants will attend an end of follow-up assessment (9th visit) which will mark the end of the trial.

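### The stated study end of December 2019 comes before any recurrence-free patient recruited from April 2019 could complete the 52-week follow-up

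*Protocol article*

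**What the plan says.** Section 4.4 (Trial status) gives three facts: "The recruitment phase began in April 2019"; "Thus far, 60 patients have been recruited"; and "The estimated end date for this study is December 2019". The planned number of patients with recurrent psoriasis is 72.

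Section 2 (Methods/design) sets out a one-week screening phase, then "an 8-week observation phase (week 1 to week 8) and a 52-week follow-up phase (week 9 to week 60". The text after Table 1 in the same section adds: "At week 60, participants will attend an end of follow-up assessment (9th visit) which will mark the end of the trial". Section 2 also says "This is a pilot randomized controlled trial for 3 years".

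Section 4.2 (Clinical efficacy evaluation basis) says that patients who reach PASI75 after 8 weeks "will be followed up and this period will start from the end of the treatment", and "If there is no recurrence, the follow-up period is 1 year". If the disease recurs, follow-up stops at the recurrence.

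Section 3.5.1 lists the recurrence rate (recurrences divided by patients followed up) and the remission period under primary outcomes. Section 3.10 names a chi-square test for the primary outcomes.

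**The concern.** Section 4.4 places the end of the study in the same calendar year as the start of recruitment, while every responder without a recurrence needs a course of more than a year. The two cannot both be right.

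The effect on relapse is the stated objective of the trial. If the date were acted on, patients would be observed for different lengths of time, all short of 52 weeks unless they had already relapsed. A crude proportion compared by a chi-square test makes no allowance for unequal or incomplete follow-up, and the remission period would be unfinished for everyone still in remission.

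**Working it through.** **Inputs.** Entry from April 2019, day not given, so 1 and 30 April are both tried (section 4.4). Study end in December 2019, taken as 31 December, the most favourable day (section 4.4). Treatment of 8 weeks plus follow-up of 52 weeks, 60 weeks or 420 days in all; 61 weeks if the screening week is added (section 2).

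**1. Can the stated date be reproduced?** Earliest week 60 = entry + 420 days.
- Entry 1 April 2019: 25 May 2020 (1 June 2020 with screening).
- Entry 30 April 2019: 23 June 2020 (30 June 2020 with screening).

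It cannot. December 2019 is about five to six months too early even for the first month's entrants.

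**2. Follow-up available by 31 December 2019.** Available follow-up = (days from entry to 31 December) / 7 − 8.
- Entry 1 April: 274 / 7 = 39.1 weeks; 39.1 − 8 = 31.1 weeks (30.1 with screening).
- Entry 30 April: 245 / 7 = 35.0 weeks; 35.0 − 8 = 27.0 weeks (26.0 with screening).

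Later entrants have less.

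**3. Working backwards.** 31 December 2019 − 420 days = 6 November 2018, about five months before recruitment opened. A patient entering after 5 November 2019 (31 December − 56 days) could not finish even the 8 weeks of treatment.

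**4. If December 2019 means the end of recruitment.** Entry on 31 December 2019 + 420 days = 23 February 2021, or 2 March 2021 with screening.

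**5. Possible size of the effect on the recurrence rate.** The article gives no recurrence rate or relapse pattern, so these are assumptions. Let p be the 52-week recurrence and assume a constant hazard. The proportion recurring by 31 weeks is 1 − (1 − p)^(31/52), and the shortfall is p minus that.

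| Assumed p | By 31 weeks | Shortfall (points) |
|---|---|---|
| 20% | 12.5% | 7.5 |
| 40% | 26.3% | 13.7 |
| 60% | 42.1% | 17.9 |
| 90% | 74.7% | 15.3 |

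The table is for the longest window anyone could have; with shorter windows the shortfall grows. If relapses cluster soon after treatment stops, it shrinks. It also assumes that patients still in remission at closure stay in the denominator as non-recurrent.

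**The case against.** The strongest reply is that this is one mislabelled date. The Trial status section is three sentences long, the other two concern recruitment, and the date is called an estimate. The design sections agree with one another on 52 weeks of follow-up to week 60, and nothing in the data management or statistical sections ties database lock or analysis to December 2019. This is a fair reading of what was probably meant, and it limits the harm: the bias arises only if the date is acted on. It does not make the date right. The section uses a separate term for recruitment and attaches December 2019 to the study itself.

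A reader might go further and infer that the one-year recurrence outcome would be observed for no patient, or that follow-up would be cut short for everyone. The article does not support that. Section 4.2 ends follow-up at recurrence, so a responder who relapses within the available weeks has a complete observation. Only responders enter follow-up at all.

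A reader might also infer a fixed minimum understatement. None can be derived, since the table moves with an assumed rate and hazard. Section 3.5.1 does not say how incompletely followed patients enter the denominator, and an analysis plan may settle that. Nor is a bias towards either arm shown, because calendar closure would apply to both by the same rule.

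**Conclusion.** The contradiction holds on every reading of the unstated days. An end in December 2019 conflicts with the 60-week schedule and with the week-60 visit as the end of the trial. The conflict with the three-year duration is supporting evidence only, because the start of those three years is not given.

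At the stated date, recurrence-free responders would have at most about 31 of 52 weeks, and nobody's one-year recurrence-free status could be confirmed, while earlier relapses would be on record. If recurrence were analysed then, the crude rate would tend to be understated and remission periods truncated. The 7.5 to 18 points quoted for assumed recurrence of 20% to 60% illustrate the scale and are not an estimate for this trial. The point deserves correction because the date governs when two outcomes listed as primary can be analysed.

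**What to change.** Reconcile section 4.4 with sections 2 and 4.2:

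- If December 2019 is the planned end of recruitment, say so.
- State the study end as the last randomised patient's week-60 visit. That is not before late May 2020 even for the first patient, and about February to March 2021 if recruitment runs to the end of December 2019.
- Analyse 52-week recurrence and the remission period only after that visit.

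The cost is a corrected date and one clarifying sentence. The follow-up is already part of the design, so no visit, patient or assessment is added.
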